	At home by mail or telephone	At the hospital Sports Valley	Start of study	At the hospital Sports Valley Week 0, week 12, and week 24	Online Week 6, week 18, and week 52	During the entire 24 weeks, daily	During the entire 24 weeks, weekly
Handover study information and informed consent	X						
Telephone call: discuss questions about participation	X						
Signing informed consent	X						
Online screening	X						
VISA-P	X						
Pain map	X						
Inclusion questions	X						
Hospital screening		X					
Physical examination		X					
Ultrasound		X					
Functional tests		X					
Explanation PTLE program		X					
Randomization			X				
Study measurements				X			
Body composition^b^				X			
Questionnaires^c^				X	X^a^		
Blood sampling				X			
Functional tests^d^				X			
Imaging^e^				X			
Myoton				X			
Compliance (sachets check)				X			
Supplement use						X	
PTLE program (3 times/week)^f^							X
Compliance							X

^a^Only the VISA-P is asked digitally in weeks 6, 18, and 52

^b^Consisting of length and body weight measurements and sevenfold sum of skinfolds measurements

^c^Consisting of the VISA-P, EQ-5D, MSK, CSI, SARS, OSTRC, and follow-up questions investigating satisfaction, return to sports, pain during activities of daily living, during sports and during the PTLE program, the use of co-interventions, compliance to exercise program and supplement intake, and investigating training load

^d^Consisting of the single leg decline squat and measurements of the isometric strength of the quadriceps, hamstrings, and abductors; muscle length; drop jump test; weight-bearing dorsiflexion lunge test; hoptests; and the squat vs countermovement jump

^e^Consisting of an ultrasound (grayscale and power Doppler) and UTC, with the ultrasound executed at 0 and 24 weeks and not at 12 weeks

^f^Part of usual care

Tendinopathy-related symptoms will be recorded at baseline and 6, 12, 18, 24, and 52 weeks’ follow-up (Fig. 1A) using the VISA-P score. At 6, 18, and 52 weeks, this outcome measurement will be determined using a web-based form. The follow-up questionnaire that is given at baseline and 12 and 24 weeks is also given at 52 weeks of follow-up.

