### Sample size {14}

The mean difference of change in VISA-P score over time between the intervention and placebo group is estimated to be 13 points higher in the intervention group compared to the placebo group. The standard deviation of the difference in VISA-P score is estimated to be 19 [15]. With a power estimated to be 80% and a significance level of 0.05, the sample size calculation (performed in G*Power 3.1.9.7) led to a total sample size of 70 participants. As we will compensate for an expected loss to follow-up of 9%, 76 participants will be included in total, i.e., 38 participants per treatment arm.

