The primary study parameter will be the difference between intervention and placebo in the change in VISA-P score (0–100) over time. The primary outcome will first be analyzed with a linear mixed model. When the residuals of the model are not normally distributed, we will use a generalized linear mixed model instead. As independent variables, the treatment (supplement or placebo), time (time points of the measured variable) and time × treatment will be fixed factors, and the participant will be used as a random factor. Adjustments will be made for those baseline variables that are associated with the primary outcome (*p* < 0.10), using a multivariable analysis and a stepwise backward elimination strategy. Examples of potentially associated variables are baseline vitamin C and collagen amino acid intake, baseline P1NP concentrations, compliance to PTLE program, compliance to supplement use, and use of co-medication. Secondary study parameters will be reported quantitatively as well, in the most commonly used way. For the secondary study parameters, we will choose between the generalized linear mixed model and the linear mixed model in the same manner as for the primary outcome. Here, as independent variables, the treatment (supplement or placebo), time (time points of the measured variable), and time × treatment will be fixed factors, and the participant will be used as a random factor. The dependent variable is the secondary study parameter in question (with as important dependent variables/outcome measures: pain during a single leg decline squat, ultrasound imaging abnormalities, UTC findings, and tendon and muscle stiffness). The same stepwise backward elimination strategy will be used as mentioned above. For parameters that are categorical (dichotomous, nominal, or ordinal) a generalized linear mixed model will be used that is applicable for that specific secondary variable (for example a logistic mixed model for dichotomous parameters, and an ordinal mixed model for ordinal parameters). For these parameters, a similar strategy will be applied as described above.

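### The primary mixed model appears to treat baseline VISA-P as an unconstrained time point, so the week-24 contrast is a raw change-score difference; using baseline better is a free gain in precision

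*Protocol article*

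**What the plan says.** The statistical methods section {20a} of the protocol article defines the target: "The primary study parameter will be the difference between intervention and placebo in the change in VISA-P score (0–100) over time". Outcomes {12} likewise makes the primary outcome a change over 24 weeks, compared between groups. The model has these fixed effects: "As independent variables, the treatment (supplement or placebo), time (time points of the measured variable) and time × treatment will be fixed factors". In addition, "the participant will be used as a random factor".

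The VISA-P schedule is under Participant timeline {13}: "Tendinopathy-related symptoms will be recorded at baseline and 6, 12, 18, 24, and 52 weeks’ follow-up". Baseline is thus one of the measured time points.

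On covariates, {20a} says: "Adjustments will be made for those baseline variables that are associated with the primary outcome" (at p < 0.10, with backward elimination). The candidates are given as examples: "Examples of potentially associated variables are baseline vitamin C and collagen amino acid intake, baseline P1NP concentrations, compliance to PTLE program", followed by supplement compliance and co-medication. Baseline VISA-P is not among them, and no common baseline mean is mentioned.

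Sample size {14} plans on the change score. The mean difference in change "is estimated to be 13 points higher in the intervention group compared to the placebo group", and "The standard deviation of the difference in VISA-P score is estimated to be 19".

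**The concern.** A time × treatment contrast measures change over 24 weeks only if baseline is a level of time. If the outcomes were post-baseline only, the interaction would measure change from week 6. With baseline in the outcome vector and a free treatment main effect, the model estimates a separate baseline mean in each arm. It does not use the fact that randomisation gives both arms the same expected baseline.

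The week-24 interaction then reduces to the raw difference in mean change. The standard error can be larger than it needs to be, and a chance baseline difference feeds into the estimate. The covariate clause does not repair this: a covariate that is constant within a participant and enters as a main effect cancels out of within-person change. The point matters most in a small trial (76 randomised, 70 evaluable planned), and the data needed to do better are already collected.

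**Working it through.** **1. The plan's own figure.** Inputs from Sample size {14}: difference 13, SD of change 19, power 80%, alpha 0.05 (taken as two-sided). A two-sample t-test with the noncentral t distribution gives 35 per arm, 70 in total, with power 80.6%; 34 per arm gives 79.4%. The stated 70 reproduces exactly. The standard error of the change-score difference is 19 × √(2/35) = 4.54.

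**2. Does the written model return the raw change difference?** 150 trials were simulated with 35 per arm, visits at weeks 0, 6, 12, 18 and 24, complete data, equal variances, correlation 0.5 between all visits and change SD 19.

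| Model | Mean SE of week-24 effect |
|---|---|
| As written, baseline a free level of time | 4.52 |
| Same, plus baseline VISA-P as a main-effect covariate | 4.52 |
| Baseline as outcome, common baseline mean | 3.91 |
| Post-baseline outcomes, baseline as covariate | 3.93 |

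The first two models matched the raw difference in mean change to within 10⁻¹² in every data set. The variance ratio of the common-mean model to the written one is (3.91/4.52)² = 0.75.

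**3. Gain with equal SDs.** Let r be the correlation between baseline and week 24. The variance ratio, adjusted to change score, is (1 + r)/2. The protocol article does not give r, so the values below are assumptions. Change SD is held at 19 with 35 per arm, and one degree of freedom is spent on baseline.

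| r | Implied SD at each visit, 19/√(2(1−r)) | Variance ratio | SE | Power for 13 points | Evaluable N for 80% |
|---|---|---|---|---|---|
| unadjusted | – | 1 | 4.54 | 80.6% | 70 |
| 0.3 | 16.1 | 0.65 | 3.66 | 93.8% | 46 |
| 0.5 | 19.0 | 0.75 | 3.93 | 90.3% | 54 |
| 0.7 | 24.5 | 0.85 | 4.19 | 86.4% | 60 |
| 0.9 | 42.5 | 0.95 | 4.43 | 82.5% | 66 |

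The last row is an end of the range rather than a scenario. Scores between 0 and 80 cannot have an SD much above 40.

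**4. Gain with unequal SDs.** Entry is capped at VISA-P below 80 (Eligibility criteria {10}) and follow-up is not, so a larger follow-up SD is plausible. With k = follow-up SD / baseline SD, the variance ratio is k²(1 − r²)/(1 + k² − 2rk).

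| k | r = 0.3 | r = 0.5 | r = 0.7 |
|---|---|---|---|
| 1.25 | 0.78 | 0.89 | 0.98 |
| 1.5 | 0.87 | 0.96 | 1.00 |

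One minus this ratio equals (1 − rk)²/(1 + k² − 2rk). It is never negative, and it is zero when rk = 1.

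An example with an assumed baseline SD of 16, change SD 19 and r = 0.5: the follow-up SD s solves s² + 16² − 2(0.5)(16)s = 19², so s = 21. The ratio is 21² × 0.75/19² = 0.92, and power is about 84%.

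**5. Chance imbalance is the same loss.** Given a baseline difference between arms, a fraction 1 − rk of it passes into the change-score difference with opposite sign. With equal SDs of 19 and r = 0.5, the baseline difference has SD 4.54, and half of it gives 2.27 points. The extra variance from step 3 is 4.54² − 3.93² ≈ 5.2, whose square root is also about 2.27. The two descriptions count one quantity.

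**The case against.** The strongest reply is that nothing here is wrong. The outcome is change, the sample size rests on the SD of change and reproduces, and the model targets change. That stands: the planned analysis is coherent and common, and it delivers its stated power.

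Three stronger readings are tempting, and the protocol article does not support them.
- A reader might infer bias from regression to the mean after selection at VISA-P below 80. Under randomisation both arms are selected alike, so the contrast is unbiased. Sensitivity to a chance imbalance is the variance loss seen conditionally (step 5), not a second harm.
- A reader might infer that the trial is too small. On its own assumptions it is not.
- A reader might take the equal-SD power figures as the expected gain. Neither r nor the two SDs are given, and step 4 shows that the gain can nearly disappear.

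It can also be said that the text never states outright that baseline is a level of time, that the covariates are only examples, and that an unseen analysis plan may settle the parameterisation. That is fair and limits the certainty of the reading. Still, {20a} does list the model terms, and they fit a change parameter only if baseline is a time point. On that reading, selecting baseline VISA-P through the covariate clause would not help (step 2).

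**Conclusion.** The point holds as a free improvement, not as an error in a stated figure. On the natural reading of Outcomes {12}, Participant timeline {13} and the methods in {20a}, the primary contrast in complete data is the raw change-score difference; with missing visits the identity is approximate. The efficiency given up lies between nearly zero and about 35% of the variance, depending on a correlation and an SD ratio that the protocol article does not report. The upper end needs equal SDs and r near 0.3; the lower end arises as rk approaches 1. Adjustment costs one or a few degrees of freedom and otherwise does not reduce precision.

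**What to change.** Before the codes are broken, restate the primary model in one of two forms:
- post-baseline VISA-P as outcome, with treatment, visit, treatment × visit, baseline VISA-P and baseline × visit; or
- baseline kept in the outcome vector, with both arms constrained to a common baseline mean.

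Name the week-24 treatment contrast as primary. Fix baseline VISA-P in the model in advance rather than leaving it to backward elimination. Use the same form for the continuous secondary outcomes, which are given the same model.

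The effect remains in VISA-P points, and the sample size need not change. The cost is a change of wording: baseline VISA-P is already collected, and no visit or measurement is added.

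### With participant as the only stated dependence term, the primary mixed model assumes equal variance and correlation across all VISA-P visits; if correlation decays, the week-24 standard error is too small

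*Protocol article*

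**What the plan says.** Section {20a} of the protocol describes a linear mixed model for the difference between arms in VISA-P change over time. Treatment, time and their interaction are fixed, "and the participant will be used as a random factor". The same sentence is used again for the secondary outcomes. The section mentions no residual covariance structure, random slope or robust standard error, and rules none out. It does not say which visits enter the model or which contrast is the primary test.

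The timing comes from other sections. Objectives {7} and Outcomes {12} set the primary outcome at 24 weeks. Participant timeline {13} has VISA-P at weeks 0, 6, 12, 18, 24 and 52; for the visits between and after the test days, "At 6, 18, and 52 weeks, this outcome measurement will be determined using a web-based form".

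Sample size {14} rests on change scores. The change "is estimated to be 13 points higher in the intervention group compared to the placebo group", and "The standard deviation of the difference in VISA-P score is estimated to be 19".

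**The concern.** A participant random intercept with independent residuals implies compound symmetry: the scores at weeks 0 and 24 are taken to be as strongly correlated as those at weeks 18 and 24, and every visit has the same variance. In balanced data the standard error of any between-visit contrast then comes from one pooled within-person variance, averaged over close and distant visits.

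The week-24 change is the longest interval among the visits up to week 24. If scores taken further apart agree less well, its true variance exceeds the pooled value. The confidence interval is then too narrow and the 5% test rejects too often. The size of the error depends on which intermediate visits are included, and the text leaves that open.

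**Working it through.** **Inputs from the protocol.** Difference 13 points, SD of change 19, alpha 0.05, power 80%, 70 evaluable and 76 randomised participants (Sample size {14}); visits at weeks 0, 6, 12, 18, 24 and 52 (Participant timeline {13}). **Assumed, because the protocol gives neither:** between-visit correlations and visit-specific SDs.

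**The plan's own figure.** The normal approximation gives 2 × (1.960 + 0.842)² × 19²/13² = 33.5, so 34 per arm. The exact two-sided t calculation needs 35 per arm (power 0.806), which is the stated 70. Allowing for 9% loss, 70/0.91 = 76.9, against 76 stated. The figure reproduces. It uses a two-sample comparison of change scores, so the covariance assumption does not enter it.

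**Formulas.** For complete data:
- true variance of the change: V(0) + V(24) − 2·Cov(0,24);
- variance used by the random-intercept model: 2 × (mean variance − mean covariance over all visit pairs);
- SE ratio: the square root of model over true;
- approximate type I error: 2 × [1 − Φ(t × SE ratio)], where t is the 97.5% point on 68 × (visits − 1) degrees of freedom.

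**Worked case.** Unit variance, with correlation 0.5^(lag/24): 0.841, 0.707, 0.595 and 0.500 at lags of 6, 12, 18 and 24 weeks. The true variance is 2 × (1 − 0.5) = 1.000.
- Five visits to week 24: mean correlation (4 × 0.841 + 3 × 0.707 + 2 × 0.595 + 0.500)/10 = 0.717; model variance 2 × 0.283 = 0.565; SE ratio 0.752; type I error 0.139 (simulated 0.141).
- Weeks 0, 12, 24: mean correlation (2 × 0.707 + 0.500)/3 = 0.638; model variance 0.724; SE ratio 0.851; 0.093 (simulated 0.096).
- All six visits: mean correlation 0.586; model variance 0.827; SE ratio 0.909; 0.074 (simulated 0.075).
- Weeks 0 and 24 only: SE ratio exactly 1.

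On the plan's own SD, the true standard error is 19 × √(2/35) = 4.54 points, a 95% half-width of 1.96 × 4.54 = 8.9. With five visits the model would report 0.752 × 4.54 = 3.42, a half-width of 6.7.

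**Simulated type I error of the week-24 contrast** (20,000 null trials, 35 per arm, two-sided 0.05):

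| True covariance | 0, 12, 24 | 0, 6, 12, 18, 24 | all six |
|---|---|---|---|
| Constant correlation 0.5 | 0.050 | 0.050 | 0.049 |
| Decay, 0.3 at 24 weeks | 0.086 | 0.127 | 0.077 |
| Decay, 0.5 at 24 weeks | 0.096 | 0.141 | 0.075 |
| Decay, 0.7 at 24 weeks | 0.100 | 0.151 | 0.067 |
| Milder decay, 0.5 at 24 weeks | 0.066 | 0.077 | 0.059 |
| Constant 0.5, SD rising 13 to 19 | 0.052 | 0.058 | 0.050 |
| Constant 0.5, SD peaking at week 12 | 0.021 | 0.021 | 0.022 |

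The milder row adds visit-specific noise: correlation 0.7 × (0.5/0.7)^(lag/24), so 0.592 at 12 weeks. For weeks 0, 12 and 24 the mean correlation is (2 × 0.592 + 0.500)/3 = 0.561, the model variance 0.878 and the SE ratio 0.937. This row accounts for the lower ends of the ranges.

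**Conservative case by hand.** SDs 13, 20, 15 at weeks 0, 12, 24, correlation 0.5. True variance: 169 + 225 − 195 = 199. Mean variance 794/3 = 264.7; mean covariance 0.5 × 755/3 = 125.8; model variance 2 × 138.8 = 277.7. SE ratio √(277.7/199) = 1.18, so the standard error is overstated.

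**Comparison test.** A t-test on the actual 0-to-24 change stays at about 0.05 in every row. The omnibus treatment-by-time F test under the decaying patterns lies between 0.054 and 0.092.

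**The case against.** The strongest reply is that section {20a} never says participant is the sole dependence term. A mixed model can carry a structured residual covariance beside a random factor, this is a condensed article, and such detail often sits in an analysis plan that is not shown. That stands as a limit on the point: it applies if the model is run as written. It does not remove the point, because the article does state a dependence term, twice, and the term it states is the restrictive one.

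A reader might go further and infer that the primary test is definitely anti-conservative, with a type I error of 10% or more. The protocol does not support that. It gives no correlations or visit-specific SDs. The model is exact under compound symmetry or with two visits, and a rising SD alone barely moves the error (0.050–0.058). A mid-study variance peak with constant correlation makes the test conservative. Figures of 10% and above arise mainly with the five visits to week 24, and the protocol does not fix that set. Nor does it fix the week-24 contrast as the test; an omnibus interaction test is less affected.

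It is also fair that the remedy was checked through a change-score t-test in complete data. No unstructured model was fitted, and nothing was run with the expected 9% loss.

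**Conclusion.** The point holds conditionally. Run as stated, the primary model assumes compound symmetry over visits spaced from 6 to 52 weeks, and nothing in the protocol supports equal correlation at short and long intervals. If correlation decays with lag to 0.3–0.7 at 24 weeks at constant variance, type I error for the week-24 contrast is about 0.06–0.08 with six visits, 0.065–0.10 with weeks 0, 12 and 24, and 0.08–0.15 with the five visits to week 24.

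These ranges belong to the assumed patterns and are not bounds. Over all the covariance patterns in the table, the true size runs from about 0.02 to 0.15. A test whose size depends this much on unstated choices is not reliably held at the 5% level the plan sets. This is a specification to tighten before unblinding, not a demonstrated error in the result.

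**What to change.** In section {20a} or the analysis plan:
- Replace the participant random intercept in the primary model with an unstructured within-participant covariance over the included visits, fitted by REML with Satterthwaite or Kenward-Roger degrees of freedom.
- Name in advance a simpler structure to use if the model does not converge.
- List the visits that enter the primary model and say whether week 52 is among them.
- Name the week-24 treatment-by-time contrast as the primary test.
- Use the same approach for continuous secondary outcomes.

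The cost is wording plus k(k + 1)/2 covariance parameters for k visits: 6 for three visits, 15 for five and 21 for six, against 2 for a random intercept. The interval may be slightly wider. Trial conduct and sample size do not change. If an existing analysis plan already says this, pointing to it settles the matter.

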## Discussion

Despite the high prevalence of PT among athletes and its potential impact on sports participation, management of (patellar) tendinopathy remains challenging. Hydrolyzed collagen and vitamin C supplementation appears to have a promising effect on the recovery of (chronic) patellar tendinopathy in combination with exercise therapy. Positive effects of hydrolyzed collagen supplementation have been found on the recovery of Achilles tendinopathy and several studies suggest an increased collagen synthesis with hydrolyzed collagen supplementation [8, 9]. In addition, vitamin C might play a role in the final step, the crosslinking of the collagen molecule, showing its importance in tendon injury recovery [10]. However, to our knowledge, no RCT has been performed yet investigating the effect of hydrolyzed collagen and vitamin C supplementation on the recovery of patellar tendinopathy. While there are not many studies on nutrition and tendon health, this is the first RCT to study the effectiveness of hydrolyzed collagen/vitamin C supplementation in combination with the PTLE program on the recovery of patellar tendinopathy in athletes. This is also the first study with the PTLE program that takes into account the training and competition load of the athletes during the entire study period using a web-based log/app. The JUMPFOOD study is one of the largest RCTs on PT. Including two additional intervention arms to disentangle the separate effects of collagen and vitamin C would make the study design more robust, but this would require an unrealistically high sample size. In addition, researchers were forced to choose block randomization to have both placebo and intervention evenly distributed throughout the year. For example, in July and August, most athletes exercise less or differently compared to when all competitions start in September, influencing their experienced PT pain.

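### Covariates for the primary and secondary models are selected by backward elimination at p < 0.10 on the trial's own outcome data, from an open list that calls post-randomisation variables baseline

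*Protocol article*

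**What the plan says.** All of this is in the Protocol article, Statistical methods for primary and secondary outcomes {20a}, unless stated.

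- **Target.** "The primary study parameter will be the difference between intervention and placebo in the change in VISA-P score (0–100) over time".
- **Model.** A linear mixed model in which treatment, time and "time × treatment will be fixed factors, and the participant will be used as a random factor". A generalized linear mixed model replaces it if the residuals are not normal.
- **Covariates.** "Adjustments will be made for those baseline variables that are associated with the primary outcome" at p < 0.10, "using a multivariable analysis and a stepwise backward elimination strategy".
- **Candidates.** "Examples of potentially associated variables are baseline vitamin C and collagen amino acid intake, baseline P1NP concentrations, compliance to PTLE program", followed by compliance with the supplement and use of co-medication. That makes six, offered as examples.
- **Secondary outcomes.** "The same stepwise backward elimination strategy will be used as mentioned above".

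The section does not say whether a selected covariate enters as a main effect or interacts with time. It names no unadjusted or fixed-covariate model as primary.

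**The concern.** Three things are wrong with the rule as written.

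1. The same data choose the covariates and then test the treatment. Backward elimination keeps variables that happen to explain residual variation, and it charges no degrees of freedom for those it discards. The final standard error is then too small, and the final model cannot be known in advance.
2. The target is a difference in change, that is, the time × treatment term. A time-fixed covariate entered only as a main effect shifts a participant's whole profile and cancels from any within-participant difference. On that reading the selection step does no useful work for the primary comparison.
3. Compliance and co-medication use are observed during follow-up and may respond to treatment. Adjusting for them can remove part of the treatment effect or break the randomised comparison. It also sits badly with the intention-to-treat principle in section {20c}, which analyses everyone irrespective of adherence.

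**Working it through.** **The plan's own figure.** Sample size {14} gives a difference of 13, SD 19, "With a power estimated to be 80% and a significance level of 0.05", and 70 participants. The normal approximation is n per arm = 2(z₀.₉₇₅ + z₀.₈₀)² × SD²/Δ² = 2 × (1.960 + 0.842)² × 361/169 = 33.5, so 34. The two-sided t-test gives 34.52, so 35 per arm, 70 in total, with power 80.6%. For 9% loss, 70 × 1.09 = 76.3 and 70/0.91 = 76.9, against the stated 76. The sample size is sound and this point does not affect it.

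**Reading A: the covariates adjust the change.** Trials were simulated with no treatment effect. The model was a linear regression on a single change outcome, with treatment forced in, backward elimination at p < 0.10 and a test at 0.05. The number of candidates is an assumption, except for six, the number the article names.

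| Candidates | Type I error |
|---|---|
| 6 | 5.7% (N = 70 and N = 76) |
| 8 | 5.9% to 6.2% |
| 10 | 6.2% to 6.4% |
| 15 | 7.6% to 7.8% |
| 20 | 7.6% to 8.2% |
| 25 | 8.8% to 9.8% |
| 30 | 11.0% to 11.2% |

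Ranges cover separate simulations with N of 70 or 76, and with either pure-noise candidates or two truly prognostic ones. With 4,000 runs, the fewest reported, the Monte Carlo standard error near 5% is √(0.05 × 0.95/4,000) = 0.34 percentage points. With 20,000 it is 0.15.

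As a control, keeping all candidates or using none gave 4.6% to 5.5%, and a fixed three-covariate model gave 4.9%. Selection is therefore the cause, not adjustment.

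The mechanism shows in the standard errors. With 25 candidates the model standard error averaged 0.229 against an empirical SD of 0.275 in one run (1 − 0.229/0.275 = 17% too small) and 0.265 in another (14% too small).

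If p < 0.10 is read as a univariable screen before the multivariable step, the error is 5.4% to 6.7%.

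*Could 25 candidates arise?* The Outcomes {12} section collects, at baseline: 3 body measures, 8 blood markers (counting lipids once), 2 decline-squat pain scores, 3 strength measures, 2 muscle lengths, 1 lunge test, 1 drop jump, 1 jump ratio and 5 hop tests. That is 26 before imaging, stiffness, diet and questionnaires. The pool exists, but nothing says that all of it would be offered to the model.

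**Reading B: main effects only, linear mixed model.** For participant i with time-fixed covariate z, the change Y(24) − Y(0) contains γz − γz = 0, so z drops out. Random-intercept models with treatment × categorical time were fitted with and without covariate main effects, on four simulated data sets per dropout level. The quantity compared is the week-24 time × treatment estimate.

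| Dropout | Movement of the estimate | Standard error |
|---|---|---|
| 0% | none to 4 decimals (for example 2.9694 both ways) | identical (4.0092 both ways) |
| 9% | 0.24 to 0.35 points | about 4.5 to 4.9, changed by less than 0.01 |
| 30% | 0.06 to 0.47 points | about 4.8 to 5.4, changed by less than 0.01 |

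The cancellation needs a linear model and a time-fixed covariate. It does not carry over to the generalized model with a non-identity link, nor to weekly compliance or co-medication entered as time-varying values.

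**The label.** Of the six examples, vitamin C intake, collagen amino acid intake and P1NP are baseline measurements. The two compliance measures and co-medication come from the weekly questionnaires in sections {11c} and {11d}, after treatment has begun. The sentence that restricts adjustment to baseline variables and its own examples contradict each other.

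**The case against.** The strongest reply is that the harm is small or absent. The model as printed has no covariate × time term, so main effects are the plain reading, and the primary test is then almost untouched. Even under Reading A, the six named candidates cost less than one percentage point. The higher figures need a candidate count that the article never gives, and they come from a single-outcome regression, not from the mixed model. A SAP may also close the list. All of this stands, and it limits the size of the point. It does not rescue the rule: a SAP that followed it would still select on outcome p-values, and under main effects the step has no purpose. Analyst blinding does not help either, because the rule needs no knowledge of which arm is which.

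A reader might infer more than the article supports:

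- *That the primary p-value and interval are too optimistic in any case.* This holds only if the covariates adjust the change.
- *That season of entry is left to the selection step.* The Discussion says that "researchers were forced to choose block randomization to have both placebo and intervention evenly distributed throughout the year", but section {20a} does not list season as a candidate. Balance over entry date is sought by design, and leaving a balanced factor out of the model generally makes the test conservative.
- *That differing covariate sets make the secondary effects incomparable.* Those outcomes are on different scales and are not directly comparable anyway.

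**Conclusion.** The concern holds in a limited form. The article fixes an outcome-driven selection rule for the primary and secondary models, and mislabels three post-randomisation variables as baseline.

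Under Reading A the type I error is about 5.7% for the six named candidates, and about 8% to 10% on the assumption of 15 to 25. A univariable screen brings it to 5.4% to 6.7%. Under Reading B, with a linear model and time-fixed covariates, the primary estimate is unaffected with complete data and moves by a small fraction of its standard error at 9% loss. The article does not say which reading applies, and neither gives a reason to keep the elimination step. The bias from adjusting for compliance or co-medication was not quantified, because it depends on how far treatment affects them.

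This is worth correcting, but it does not undermine the design.

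**What to change.** 1. Delete the p < 0.10 backward elimination from the primary and secondary models.
2. Name a short list of covariates, kept whatever their p-values: the outcome's own baseline value and at most one or two prognostic factors such as symptom duration. Calendar season of entry is optional. Adjusting for randomisation block is dearer: 76/8 = 9.5, so about 10 blocks and 9 degrees of freedom. All must be fixed before treatment can influence them. The Participant timeline {13} places the baseline test day after allocation, so the wording should require values taken before the first dose.
3. State how they enter. If baseline VISA-P is a covariate, remove week 0 from the response; otherwise keep week 0 and constrain the arms to a common baseline mean. Give the other covariates time interactions so that they adjust the follow-up or change estimate.
4. Exclude compliance and co-medication use from the primary model. Any analysis using them should be labelled supplementary.

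The cost is a change of wording and a few degrees of freedom. It should be settled before the treatment codes are broken.
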